#### Primary and secondary outcomes

The *primary outcome* is the maximum walking distance (MWD), defined as the distance at which the patient cannot continue walking due to pain. The primary outcome is chosen as it represents a central limitation for patients suffering from IC and will further allow us to compare to the existing evidence [2, 6, 7, 26].

*Secondary outcomes* include pain-free walking distance (PWD), defined as the walking time at which the patient first experienced claudication pain and the Vascular Quality of Life Questionnaire (VASCUQoL-6), an instrument to determine HRQoL in patients with PAD. MWD and PWD are measured through a graded treadmill test as described in the Gardner protocol [30]. Both primary and secondary outcomes are measured at baseline, 12 weeks from baseline and 6 months from end of intervention.

#### Other outcomes

Through the REDCap database, Patient Reported Outcome Measures (PROM) questionnaires will be sent to participants’ digital safe mail at baseline, at 12 weeks and 6 months from end of intervention. Questionnaires will be answered online by the participants and responses are stored automatically in the database upon submission.

#### Maintenance and integration into daily life

The achieved results of exercise and lifestyle interventions tend to decrease over time if changes are not successfully integrated into the participant’s everyday life [39, 40]. Physiotherapists will ask the participants (documented in the REDCap database) at the end of the intervention and 6 months from end of intervention, about the integration and maintenance of exercise and will offer motivational advice to support lifestyle changes. Furthermore, municipalities are encouraged to bring in other community stakeholders in this process, such as patient associations, sports associations, and voluntary groups to assist in the transition from supervised exercise to exercising as a part of everyday life.

#### Harms and dropout

Supervised exercise training is considered safe for patients with IC with a low all-cause complication rate [41]. Information on adverse events during the intervention or dropout from SET, and the cause e.g. death, surgery etc. is registered by the physiotherapists in the REDCap database. At 6 months from end of intervention, the participants will receive an electronic questionnaire concerning contact with the hospital or the general practitioner for further registration of harms. Adverse events will be categorized as serious and non-serious according to the Food and Drug Administration definition [42].

#### Performance indicators

The defined performance indicators are inspired by quality indicators from similar databases and interventions, e.g. the Danish Cardiac Rehabilitation Database [43, 44], smoking cessation data [45] and the Danish Population Survey on Health 2021 [46] as well as research studies on IC [2, 7, 26]. All indicators were debated with stakeholders and if necessary, changed before they were finally decided upon. The performance indicators help ensure a steady assessment of the implementation process and secure a continuous evaluation as recommended by the ADAPT guideline [14].

Performance indicators [47] were presented and discussed and 16 performance indicators were agreed upon by stakeholders from the municipalities and the Department of Vascular Surgery at SUH (surgeons, managers of the physiotherapists, health consultants, smoking cessation consultants and clinical physiotherapists). Of the 16, five are chosen as key performance indicators (KPI). All performance indicators can be found in the (S2 Table), while Table 3 displays the five KPIs. We will evaluate KPIs every three months and all performance indicators every six months for a minimum of four years. As the implementation process proceeds and develops, we may adjust the performance indicators accordingly or add other variables in line with ADAPT guidelines to ensure well-informed adaptations of the intervention into practice [14]. Furthermore, the KPI’s are monitored and if below the thresholds they will be discussed with the stakeholders and initiatives can be initiated to raise the KPI’s. KPI’s will be evaluated both across municipalities and for each municipality separately. If it is possible to reach a high enough number of participants in each municipality, effect evaluation will further be done for each municipality.

**Table 3 pone.0315577.t003:** Key performance indicators.

Indicator category	Indicator definition	Sector	Type	Standard
**Referral**	1. Proportion of patients with IC consulted at dept. of vascular surgery referred to municipality-based SET training program	Hospital	Process	≥50%
**Enrollment**	2. Proportion of referred patients with IC enrolled in a SET training course and registered in the database with baseline tests.	Municipality	Process	≥90%
**Retention**	3. Proportion of patients with IC with available baseline tests who complete the program with clinical tests at 6-mo. follow-up (from end of intervention)	Municipality	Process	≥60%
**Questionnaire compliance**	4. Proportion of patients with IC with completed baseline questionnaire who complete and return the 6-mo (from end of intervention) follow-up questionnaire	Municipality	Process	≥60%
**Walking distance**	5. Proportion of patients with IC who increase their MWD from baseline until 6-mo. follow-up (from end of intervention) with a minimum of 120%	Municipality	Result	≥50%

SET, Supervised Exercise Training; IC, Intermittent Claudication; MWD, Maximum Walking Distance.

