## Introduction

### Background and rationale

More than 200 million people worldwide have peripheral arterial disease (PAD) [1]. PAD is an arterial occlusive disease caused by arteriosclerosis. The consequences for people with PAD may be a progression from asymptomatic disease to intermittent claudication (IC), critical limb ischemia and finally amputation [2]. Progression of the disease entails a negative impact on health-related quality of life (HRQoL) and can eventually lead to death [2]. Patients with IC have a five-year all-cause mortality rate of 10–15% and a 20% chance of a non-fatal cardiovascular event [3]. When IC progresses to critical limb ischemia, an even higher mortality rate of 25% after one year has been reported [4].

The common treatment regime for IC is walking advice, medical treatment and surgical intervention, mainly endovascular revascularization for progressive PAD [2]. However, early revascularization is associated with a greater risk of subsequent requirement for major amputation than initial conservative treatment [5].

The European guidelines recommend supervised exercise therapy (SET), smoking cessation and a healthy diet for individuals with PAD [6]. These components can increase walking distance, reduce leg pain, minimize the need for an operation and improve HRQoL in people with IC [2, 7–9]. Only when daily activities are severely compromised should revascularization be considered [6].

Despite the evident impact of SET on IC, [2] implementation remains scarce in most European countries [10]. A survey from 2019 showed that 96% of vascular surgeons in Denmark would refer their patients to SET if it was accessible [11]. Despite this, only 14% of the 98 municipalities in Denmark provide systematic SET targeting IC [11] leaving the majority of Danish patients with simple advice on ways to increase physical activity by themselves, with no professional supervision [11]. A cost-benefit analysis of the implementation of a stepped care model consisting of primary SET treatment followed by revascularization in case of SET failure found significant potential annual savings in Dutch healthcare resources between 3.9–33.0 million euros [9]. Altogether, this highlights the potential impact on patients and society of implementing SET for people with IC.

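### KPI 5 credits any walking gain that meets its 120% threshold at 6 months whatever its cause, so gains after revascularisation count as programme success

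*Protocol article*

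**What the plan says.** In the protocol article, Table 3 (Performance indicators) gives KPI 5 as the proportion of patients with intermittent claudication "who increase their MWD from baseline until 6-mo. follow-up (from end of intervention) with a minimum of 120"%. The row labels it "Municipality Result ≥50"%. It is the only one of the five KPIs typed as a result; the other four are process indicators. It is built on maximum walking distance (MWD), the primary outcome.

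The same section has the KPIs evaluated every three months, across municipalities and for each one separately. It adds that "the KPI’s are monitored and if below the thresholds they will be discussed with the stakeholders", after which initiatives may follow.

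Surgery and hospital contact appear elsewhere:

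- Harms and dropout: "dropout from SET, and the cause e.g. death, surgery etc. is registered by the physiotherapists in the REDCap database".
- Harms and dropout, at 6 months after the intervention: "the participants will receive an electronic questionnaire concerning contact with the hospital or the general practitioner for further registration of harms".
- Table 2: a patient-reported item on hospitalisation or other doctor contact, at 12 weeks and 6 months.

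None of these places refers to KPI 5, and KPI 5 refers to none of them.

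**The concern.** KPI 5 is meant to show what the municipal exercise programme achieves. Its definition looks only at two walking tests and not at what happened between them. Revascularisation in that interval can lengthen walking distance by itself, and the indicator cannot tell such a gain from one obtained by exercise.

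The event is foreseeable. Patients are recruited from a vascular surgery department, and surgery is one of the article's own examples of a reason for dropout. Background and rationale says the recommended components can "increase walking distance, reduce leg pain, minimize the need for an operation and improve HRQoL in people with IC", and it describes a Dutch stepped-care model of "primary SET treatment followed by revascularization in case of SET failure". An indicator that credits walking gains after an operation sits awkwardly with that rationale.

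What is at stake is how a KPI 5 value is read. A municipality with weak exercise results could stay above the standard, and so not prompt the discussion, because more of its participants were operated on. Two municipalities could also differ on KPI 5 for reasons unrelated to how they deliver exercise.

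**Working it through.** **No figure to reproduce.** The 50% standard was agreed with stakeholders, not calculated, and the article gives no revascularisation rate. The arithmetic below is sensitivity only.

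**Inputs**
- Standard: 0.50 (Table 3).
- r = share of participants tested at 6 months who were revascularised after baseline. Assumed, 5% to 20%.
- p = share of non-revascularised participants reaching the threshold. Assumed, 0.45.
- q = share of revascularised participants reaching it. Assumed, 0.90, then varied.

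**Formulas**
- (a) As printed: (1 − r)p + rq.
- (b) Revascularised counted as not reaching the target: (1 − r)p.

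**Results with p = 0.45, q = 0.90**

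| r | (a) as printed | (b) counted as not reached |
|---|---|---|
| 5% | 0.95 × 0.45 + 0.05 × 0.90 = 47.3% | 42.8% |
| 10% | 0.90 × 0.45 + 0.10 × 0.90 = 49.5% | 40.5% |
| 15% | 0.85 × 0.45 + 0.15 × 0.90 = 51.8% | 38.3% |
| 20% | 0.80 × 0.45 + 0.20 × 0.90 = 54.0% | 36.0% |

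At r = 10%, version (a) is still just below the standard. It reaches 0.50 at r = (0.50 − p)/(q − p) = 0.05/0.45 = 11.1%, where (b) is 0.889 × 0.45 = 40.0%.

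**Dependence on the assumptions**
- p = 0.45, q = 0.60: r = 0.05/0.15 = 33%.
- p = 0.45, q = 0.80: r = 0.05/0.35 = 14%.
- p = 0.45, q = 1.00: r = 0.05/0.55 = 9%.
- p = 0.40, q = 0.90: r = 0.10/0.50 = 20%.

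**Starting from an observed KPI 5 of exactly 50%.** Version (b) is then 0.50 − rq. For q from 0.6 to 1.0 it is 47.0% to 45.0% at r = 5%, 44.0% to 40.0% at r = 10%, and 38.0% to 30.0% at r = 20%.

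**Single municipality.** Take 50 tested participants (assumed), p = 0.45 and q = 0.90. The binomial chance of showing at least 50% is 0.53 under (a) and 0.11 under (b) at r = 10%. At r = 20% it is 0.76 and 0.03.

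**What the existing data can cover.** Registration of surgery as a dropout cause concerns participants who leave the programme. The period after it relies on patient questionnaires, and the KPI 4 standard for returning the 6-month questionnaire is 60%. That standard is met with up to 40% of these questionnaires missing.

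**The case against.** The strongest reply is that KPI 5 is a pragmatic monitoring indicator. An all-cause result is a legitimate thing to monitor, missing the standard leads to discussion rather than sanction, and the article allows indicators to be adjusted. The full indicator list (S2 Table) and the analysis plan are not shown and may carry a rule. Every rate in the illustration is assumed, and a p just under the standard makes crossing easy. All of this stands, and it limits the point to what Table 3 prints and how that can be read.

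Several stronger readings are tempting, but the documents do not support them:

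- *Any improvement counts.* It does not; there is a 120% threshold. Whether this means to or by 120% is a separate question, and the present point holds either way.
- *Every revascularised participant counts as a success.* Only one who has the 6-month test and reaches the threshold does. KPI 3 ("Proportion of patients with IC with available baseline tests who complete the program with clinical tests at 6-mo. follow-up (from end of intervention") expects at least 60% of participants with baseline tests to have that test. Someone who leaves for surgery may not, and KPI 5 does not say how untested participants enter the denominator.
- *Surgery after the programme goes unrecorded.* Hospital contact is asked. The gap is that revascularisation is not named in the items shown and the answers are not tied to KPI 5.
- *KPI 5 is the programme's only result indicator.* It is the only one among the five KPIs. There are 16 performance indicators, and Table 2 also marks pain-free walking distance as one.
- *Surgery after baseline means the exercise therapy failed.* That sequence describes the Dutch model. Avoiding operations is not among this article's stated objectives, and patients with earlier vascular surgery may enter.
- *The planned 6-month MWD effect analysis is contaminated.* How it handles revascularisation is a matter for the analysis plan, and its absence here is no fault.

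**Conclusion.** The point holds in a limited form. Table 3 fixes the KPI 5 definition and standard for three-monthly use, and nothing shown excludes or flags participants revascularised between the two tests. A value at or above 50% therefore cannot be read as gains from exercise therapy alone.

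The size is unknown. Under the main assumed rates, the counting rule decides whether the standard is met once about 11% of tested participants are revascularised; under the other values tried, that point lies between 9% and 33%. This shows that the rule can matter. It is not an estimate of bias in this cohort. Counting revascularised participants as not reaching the target is one defensible rule among several, so the case is for showing both figures rather than replacing one with the other.

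**What to change.** Add to the KPI 5 row of Table 3 that the indicator is reported, overall and for each municipality, in two versions:

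- (a) as now;
- (b) with participants revascularised between baseline and the 6-month test counted as not reaching the target.

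Show the proportion revascularised beside the two figures. Use one stated denominator for both versions, so that they differ only by the counting rule.

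Identify these participants from the surgery and hospital-contact data already collected. Confirm them where possible with the Department of Vascular Surgery, which is a partner in the project and whose patients KPI 1 already covers.

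The cost is a sentence in the table and a small data linkage, whose availability to the project database the article does not establish. Version (b) will be somewhat less favourable whenever a revascularised participant reaches the threshold. Clinical management does not change.

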#### Qualitative investigation

Qualitative methods are applied to enhance our understanding of the pitfalls of the implementation process and what works well from the users’ perspectives. We will investigate experiences and acceptability with the intervention among patients and physiotherapists. We will focus on the user’s experiences with experienced barriers and facilitators and investigate how the patients transfer the lifestyle change into their everyday lives, to be able to make improvements in the various components during the first two years.

Two qualitative studies are planned. The scientific philosophy underpinning these studies is hermeneutic as we wish to understand and interpret experiences within both the intervention and the implementation process [48]. As such, the qualitative studies add perspective and nuances to the quantitative data collected.

The first qualitative study is an interview study to gather knowledge of the patients’ experiences with SET. This study will use semi-structured, in-depth, individual face-to-face interviews [49] with patients followed by a thematic analysis [50]. The semi-structured guide is developed with participation of the physiotherapist, and includes the following questions: How does the patients experience the SET? Has it had a meaning in the patients’ everyday lives and how can the intervention be refined? Inclusion criteria are the patients’ completion of the SET, including baseline and 12-week tests. The patients are recruited at the first appointment with the physiotherapist at their local centre and contacted later by a researcher for the interview. The intention is to include a representative sample of participants from each municipality.

The second qualitative study will aim to explore the causes of dropout and factors that can facilitate participants’ enrolment or stay in the SET.

The study will be done through a semi-structured, in-depth, individual interview study with participants and subsequently, a focus group [51] with physiotherapists incorporating these participant perspectives as themes and discussing them in the focus group to provide further insights on circumstances for dropping out, followed by a thematic analysis [50]. To address the anticipated challenges in commuting due to their IC, this study will use individual interviews with participants in their own home or via telephone [49]. Inclusion criteria for participants are the participant’s dropout at any time in the SET and inclusion criteria for physiotherapists are experience with supervising SET. The participants are recruited at the first appointment with the physiotherapist at their local center and contacted later by a researcher for the interview. The physiotherapists are contacted by interviewer during the implementation process. To develop the semi-structured guide, we will work with a panel of patients to provide insights from a user perspective [18].

#### Organizational data

Yearly, we will collect information from each municipality retrospectively. This is to map the different political organizations in each municipality and to investigate the organization of their specific IC intervention and the associated impact, resources and costs. An electronic questionnaire will be developed in the REDCap database, and each rehabilitation manager of the municipality will be the recipient. The focus is on conveying how each municipality conducts SET for participants with IC. This questionnaire has two main aims: 1) evaluate the impact that the organization has on effect, and 2) conduct cost-benefit analyses of the implementation of SET for people with IC. The questionnaire encompasses e.g. the specifics on resources (personal and location) spent in association with the SET intervention and how maintenance is secured post-SET intervention.

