#### Setting of implementations

The SET intervention and smoking cessation will take place in a municipal setting, geographically close to where people with IC live. The period for recruitment is 1 Sept. 2023–31 Dec. 2025. The intervention was inspired by the studies of Hageman et al., Murphy et al. 2008 and Murphy et al. 2012 [2, 7, 16]. Denmark is divided into five regions, each divided into a number of municipalities with a different number of local healthcare centers. These centers hold a main responsibility for rehabilitation services in Denmark. The 17 municipalities in the Region of Zealand are organized into four clusters that facilitate political and strategic intersectoral collaboration. To accommodate this organizational structure and ensure a geographical distribution, a minimum of one municipality in each cluster will be included in the pilot phase. The implementation process outlined in this protocol consists of three phases, as depicted in Fig 2. The first phase, known as the pilot phase, includes five municipalities and is expected to take place in 2023 and 2024. The second phase expected to take place in 2024, focuses on including the rest of the municipalities, where some municipalities have more than one rehabilitation site. Finally, in the third phase, the implementation of SET becomes a part of routine practice in the municipalities and the focus is on maintaining the adapted intervention. This phase is thought to run throughout 2025 and forwards.

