#### Intervention

The SET intervention design is based on the existing evidence on SET for people with IC [2, 6, 7, 16, 25], international guidelines [6], and the experiences from existing interventions in the Southern Region of Denmark [26] and adapted to the context in which the intervention is being implemented in Region Zealand. Each exercise session is supervised in a local healthcare setting as this is found superior to structured home-based exercise therapy and simple walking advice [2]. Further, studies show that exercising in a supervised compared to an unsupervised setting provides further improvement in maximal walking distance and quality of life [7, 8, 27, 28].

The intervention is as follows:

*Exercise duration and frequency* [2, 6, 25]: 12 weeks supervised exercise training program with three supervised exercise sessions per week. Every session on the treadmill consists of 5 min warm-up, 50 min walk, and 5 min cool down.*Modality*: The exercise takes place mainly on the treadmill. The patient must be pushed to walk until they reach 3–4 on the claudication pain scale and then break until the pain are reduced to a minimum (pain score 1) [2, 6].*Smoking cessation*: Smoking cessation is essential, and all participants should be screened, and smokers should be referred to smoking cessation [6].*Healthy diet*: Guidance to a healthy diet is recommended [6]

Participants are assisted by the physiotherapists in making sustainable plans for future physical activities at the end of the supervised intervention, to maintain the results achieved.

The SET intervention is adapted with guidance from the ADAPT framework [14], with a focus on adaptions to improve intervention-context fit, while maintaining consistency with intervention functions [14].

The intervention is adapted in the following ways: 1) we include participants who are challenged by medical diseases and co-morbidities. Participants not able to walk on the treadmill may attend other types of supervised exercises e.g. cycling. Throughout the intervention the physiotherapists will assess if a participant has raised a suitable capability to walk on the treadmill. 2) The intervention is flexible within the duration, modality and frequency of the SET to meet the organizational setup in each municipality described in more detail below.

The TIDieR checklist has guided the description of the SET intervention [29] as displayed in Table 1.

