The implementation process is planned as flexible and iterative with high stakeholder involvement. When allowing flexibility in the implementation, a plan is necessary for monitoring and securing the quality of the intervention [14]. We therefore plan to conduct a process evaluation to examine the success of the implementation strategy itself [55]. In this, we plan to describe the relationship between interventions and context [14, 56] as we are aware that the inclusion of several healthcare sites may lead to different adapted versions of SET. The process evaluation will address the overall implementation by translating scientific results into practice as a whole and stratified for each of the included municipalities [57]. The process evaluation will follow the MRC framework for conducting and reporting process evaluation studies [57]. In the analyses, cross-cutting qualitative and quantitative results on the implementation (adherence, dose, quality of delivery, participant responsiveness and reach) will be synthesized to gain knowledge on how the implementation is delivered and implemented [58]. An expected barrier that may limit our implementation process is the fact that the SET intervention is facilitated from one sector, the Region, and executed in the municipalities, another sector. However, the cost of the intervention lies in the municipalities and not the hospitals. Another limitation that may interfere with the implementation is the use of treadmills. Even though two treadmills per municipality are financed through this project, the treadmills still require a lot of space, and it can take time for the participants to get acquainted with treadmill walking. Further it is not always possible for participants to continue treadmill walking after SET.

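### Organisation, the exposure for the aim of relating organisation to effect, is recorded once a year, in retrospect and per municipality, so some patients may be matched to arrangements that did not apply during their course

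*Protocol article*

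**What the plan says.** The Organizational data section sets the method: "Yearly, we will collect information from each municipality retrospectively". The questionnaire will be built in REDCap, and "each rehabilitation manager of the municipality will be the recipient". It has two main aims. The first is to "evaluate the impact that the organization has on effect"; the second is a cost-benefit analysis.

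Other sections bear on whether one answer per municipality per year is enough:

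- Setting of implementations describes a second phase bringing in the remaining municipalities, "where some municipalities have more than one rehabilitation site".
- The Discussion recognises that "inclusion of several healthcare sites may lead to different adapted versions of SET".
- Performance indicators: "We will evaluate KPIs every three months and all performance indicators every six months for a minimum of four years". On the key indicators it adds that "if below the thresholds they will be discussed with the stakeholders and initiatives can be initiated".
- Objective, Stakeholder involvement and Qualitative investigation all foresee refinement of delivery while the programme runs.
- Table 1 (items 10 and 12) says that modifications are monitored and reported. Table 2 has patients report the duration and frequency of rehabilitation at 12 weeks.

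**The concern.** The questionnaire is the named source of an exposure for an effect question, not just background description. An exposure has to be true of the patient at the time of that patient's course. Here it is collected at a coarser level than the site where the patient trains and at longer intervals than the programme's own review cycle, and it relies on looking back over the year.

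If two sites in a municipality run SET differently, or if one site changes its arrangements partway through a year, some patients may be analysed under arrangements they did not have. A comparison of ways to organise SET could then understate a real difference, or in less benign circumstances create or reverse one. Dates and site details that nobody wrote down at the time cannot be fully recovered by later analysis, so this belongs to data collection and cannot wait for the analysis plan.

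**Working it through.** The protocol gives no figure on this point to reproduce. The check compares recording intervals, then sizes the possible error under stated assumptions.

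**1. Review cycle against recording cycle.** Recruitment runs from 1 September 2023 to 31 December 2025, which is 28 months. Key indicators are read every 3 months and organisation every 12.

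- Indicator readings per organisational record: 12/3 = 4.
- Over recruitment: 28/3 ≈ 9 readings against 28/12 ≈ 2.3, so two or three yearly records.

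**2. Patients affected by one change in one municipality.** Assume steady enrolment over the year, one change after month *t*, and a form that records only the year-end state. The share of that year's patients who started under the earlier arrangement is *t*/12:

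- *t* = 3, 6 or 9 gives 25%, 50% or 75%, with a mean of 50%.
- With a 12-week course, up to 12/52 = 23% of the year's patients would be mid-course at the change.
- If the form instead records the state that held for most of the year, and the change falls at a uniformly random time, the mean share is 25%. If it asks for dates of change, the share is about 0.

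One answer covering two equal-sized sites that are organised differently would likewise misplace half of that municipality's patients.

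**3. Effect on a comparison.** Take a two-level organisational factor with true means A and B, and let the same share *p* be misassigned in each group, unrelated to outcome. The observed difference is

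[(1−*p*)A + *p*B] − [(1−*p*)B + *p*A] = (1−2*p*)(A−B).

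Let *m* be the share of municipalities that change once in a year. With the 50% mean from step 2, *p* = 0.5*m*:

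| Municipalities changing (*m*) | Misassigned (*p*) | Contrast kept (1−2*p*) |
|---|---|---|
| 0% | 0% | 100% |
| 10% | 5% | 90% |
| 25% | 12.5% | 75% |
| 50% | 25% | 50% |

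The documents do not give *m*. The table shows a range and is not an estimate.

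**4. When the error is related to outcome.** Indicator 5 in Table 3 is improvement in maximum walking distance, and indicators are evaluated per municipality and discussed with stakeholders. A change may therefore be prompted by poor results. A form recording only the later state could then credit the earlier poor results to the new arrangement. Managers may also answer after seeing their own results. The formula in step 3 does not cover this, and the direction of bias is open. The first route is narrowed by timing: indicator 5 is read 6 months after a course of normally 12 weeks, about nine months from start, so the patients behind a low reading may belong to the previous year's form.

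**5. What other sources cover.**

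| Feature | Other source stated in the protocol |
|---|---|
| Duration and frequency | Patient report at 12 weeks (Table 2) |
| Modifications to SET | Monitored and reported (Table 1, items 10 and 12); date, site and patient link not stated |
| Individual or group format (Table 1, item 6) | No dated, site-level source stated |
| Smoking-cessation format | Acceptance is recorded per patient (Data collection); no dated, site-level source for format |
| Resources, location, post-SET maintenance arrangements | Yearly questionnaire only |

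**The case against.** The strongest reply is that the protocol records organisation at the level where it says organisation varies: "The intervention is flexible within the duration, modality and frequency of the SET to meet the organizational setup in each municipality". Supervised exercise therapy and Organizational data also speak of municipalities. On that reading, the unit of record and the unit of variation agree.

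The questionnaire is also still to be developed, and its content is given only by example. It could ask about each site and date each change, and a retrospective answer may draw on rosters rather than memory. A condensed article may leave form fields and linkage rules to the full protocol, database specification or analysis plan. In addition, four of the five key indicators are process measures (referral, enrolment, retention, questionnaire return), and acting on them need not alter how SET is delivered.

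Much of this stands. A reader might infer that sites within a municipality do differ, that changes do follow the quarterly readings, and that patients will be linked to the wrong version of SET. The documents support none of these as fact. Several sites may lead to different versions, initiatives can be started if an indicator falls short, and no rule linking patients to organisational data is stated.

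What the reply does not remove is that the yearly interval, the retrospective collection and the municipal respondent are written into the protocol. The Discussion itself raises differences between sites, and the programme is meant to be adjusted as it goes. A form answered once per municipality cannot show whether its sites differ unless it is built to ask.

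**Conclusion.** The point holds as a risk, not as a demonstrated error. The stated method for recording organisation is coarser than the question it serves, and some patients may be matched to arrangements that did not apply to them. Duration and frequency are partly protected by patient reports, and modifications may be protected if that monitoring is dated and by site.

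The size is unknown and could be nil. The figures of 90%, 75% and 50% of a contrast retained rest on four assumptions that the documents do not supply: the rate of change, year-end recording, a two-level factor, and error unrelated to outcome. It would be tempting to conclude that the flaw simply pulls differences toward zero. That holds only under the last of these assumptions; if poor walking-distance results prompt the changes, the bias may go either way.

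This affects a stated aim but not the measurement of the primary outcome. It is a cheap improvement that should be made while the form is being built.

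**What to change.** - Have the organisational form in REDCap answered per rehabilitation site rather than once per municipality.
- Add a short change log in which each site enters the date and nature of any change in frequency, duration, modality, group format, smoking-cessation programme, resources or maintenance arrangements. Complete it when the change occurs, and at the latest at each three-monthly indicator review. If the existing modification monitoring already holds dates and sites, extend that instead of starting a second record.
- Store the site identifier in each patient file, and link organisation to patients by site and start date. The analysis plan can then say how courses that straddle a change are classed.
- Keep the yearly form to managers for costs.

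The cost is one site field, a brief log in the existing database, and a few minutes per site per quarter.
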